### Study Overview

The Bread Related Effect on Microbial Distribution study was a double-blinded, placebo-controlled, crossover randomized controlled trial of healthy adults with low DF intake. The design and management of the clinical study adhered to the CONSORT (Consolidated Standards of Reporting Trials) guidelines [45]. This design accounts for the recognized variability in individuals and enables each participant to be their own control for their assigned interventions [46,47]. The study duration was a nominal total of 14 weeks, consisting of a 2-week lead-in phase, two 4-week intervention phases separated by a 2-week washout phase, and a final 2-week follow-up phase (Figure 1). During the first intervention period, one group of participants consumed 3 slices (for female individuals) or 4 slices (for male individuals) of DRB-fortified bread daily for 4 weeks, whereas the other group consumed placebo bread. Following a 2-week washout period, participants who consumed the fortified bread in the first period crossed over to consume placebo bread in the second period, and vice versa (Figure 2). Participants were instructed not to alter their diet during the 2-week washout period. The washout period was selected based on gut microbiota studies reporting a return of microbiota abundances to baseline level within 2 weeks after the intervention [48].

Before study commencement, a mutually agreed schedule was discussed and set with each participant to ensure that they understood all expected clinic or visit times and the study timeline. However, when a participant could not come to the clinic on the day a phase was ending, the participant’s needs were accommodated by allowing for earlier visits to the clinic for up to 3 days before the end of the intervention phase (minimum of 25 days of the 28-day intervention). This approach reduced the risk of participants exhausting intervention supplies before the visit and noncompliance or dropout due to scheduling issues.

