#### Statistical Analysis Plan

This study was conducted as a superiority trial. The guidelines of the Committee for Proprietary Medicinal Products (now termed Committee for Medicinal Products for Human Use) require intention-to-treat analysis [93]. For a crossover design, the intention-to-treat analysis means that every enrolled participant who has consumed both the intervention and placebo bread is included despite dropout or noncompliance. All data from randomized participants who received at least one intervention dose and had at least one postintervention measurement will be analyzed.

The mean differences from the baseline of most outcomes will be compared between groups and referred to as a between-group comparison. For most outcomes, within-group analysis (after the intervention compared with baseline) will also be performed. For metabolome analyses, postintervention values (not the mean differences) will be compared within and between groups.

All statistical analyses will be performed using SPSS statistics (version 29; IBM Corp) or R (version 4.3.1) by blinded researchers under the guidance of an independent biostatistician.

Baseline characteristics will be presented using descriptive statistics. The mean and SD, or median and range, will be used to describe continuous variables. Frequencies or percentages will be used to describe categorical variables. The group effects (ie, the mean change from baseline between groups) will be assessed using (parametric) 2-tailed *t* tests and (nonparametric) Mann-Whitney or Kruskal-Wallis tests for symmetrically and asymmetrically distributed data. Categorical variables will be assessed using chi-square tests (or Fisher exact tests for small samples). A 2-tailed *P*<.05 is determined as statistically significant. A value of *P*≤.10 will be considered a trend for most variables except for the microbiome data.

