As mentioned previously, the comparisons will be between each group and baseline and between groups after the intervention for plasma or fecal metabolome measures. The partial least squares projection discriminant analysis (PLS-DA) model will be performed to identify metabolites using SIMCA (version 17; Umetrics). The PLS-DA models will be subject to 100-fold permutations to evaluate performance; the models will be validated using the predictive ability of the model (Q2) and the ANOVA testing of cross-validated predictive residuals (ANOVA testing of cross-validated predictive residuals) [94]. The most discriminating features will be selected for building PLS-DA models. These models will be again subjected to prediction accuracy and overfitting assessment by the corresponding tests (ANOVA testing of cross-validated predictive residuals) and comparison of the Q2 afterward. Features will be selected based on their variable importance in the projection score. Univariate statistical analysis and heat maps will be performed using MetaboAnalyst (version 5.0) [95]. The metabolite and lipid relative intensity differences between groups will be tested through *t* tests or Wilcoxon rank sum tests. The multiple testing corrections will be controlled using FDR correction [96].

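### Metabolome PLS-DA is specified without participant structure in a crossover; if validated by sample, Q2 is biased downward and weak bread effects can be missed

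*Protocol article*

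**What the plan says.** Study Overview describes a two-period crossover: "participants who consumed the fortified bread in the first period crossed over to consume placebo bread in the second period, and vice versa". It justifies the design because it "enables each participant to be their own control for their assigned interventions".

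The Statistical Analysis Plan then sets within-person change aside for this outcome: "For metabolome analyses, postintervention values (not the mean differences) will be compared within and between groups". Its metabolome paragraph adds that each bread is also compared with its own baseline. The model is PLS-DA, fitted in SIMCA. On validation it says "The PLS-DA models will be subject to 100-fold permutations to evaluate performance" and "the models will be validated using the predictive ability of the model (Q2) and the ANOVA testing of cross-validated predictive residuals". A second round follows: "The most discriminating features will be selected for building PLS-DA models", with selection by variable importance, and the rebuilt models are assessed again by CV-ANOVA and Q2. Univariate comparisons use t tests or "Wilcoxon rank sum tests", with FDR correction.

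No paired or multilevel form of PLS-DA is named. No fold unit, number of folds, permutation unit or cut-off for Q2 or CV-ANOVA is given. By contrast, the same section names the paired signed rank test for the primary microbiome composite.

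**The concern.** Ordinary PLS-DA treats every sample as an unrelated unit. Here each completer's samples come in pairs with opposite labels: DRB against placebo, or baseline against post-intervention. People differ persistently in their metabolites, so the training sample most like a held-out sample is often its own partner, and the partner carries the other label. The model partly recognises the person and leans towards the wrong bread.

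Two things follow if validation is by sample. Q2 falls below what the true bread effect would give, and freely shuffled labels no longer resemble the real labelling, so the permutation P value has the wrong reference. At stake is the metabolome part of secondary aim 4. The daily fiber contrast is 8 − 2.7 = 5.3 g for women and 10.6 − 3.6 = 7.0 g for men over 4 weeks in healthy adults. A weak metabolite effect is therefore conceivable, although the article gives no expected size.

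**Working it through.** **Inputs from the article.** 56 participants analysed (Results); both breads per completer (Study Overview); post-intervention values, PLS-DA, permutation, Q2 and CV-ANOVA (Statistical Analysis Plan). The article states no Q2 or detection figure, so there is none to reproduce.

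**Assumptions not in the article.** 7 folds, 200-300 independent features, 10% of them shifted by 0 to 0.8 SD, between-person share of variance (ICC) 0.3 to 0.7, one or two components, permutation P ≤ .05 counted as detection.

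**Step 1: the structure.** 56 × 2 = 112 samples, 56 per label. With 7 folds by sample, each fold holds 112 / 7 = 16. The chance that a held-out sample's partner is in training is 96 / 111 = 0.86, and that partner always has the opposite label. After free label shuffling, a partner has the opposite label with probability only 56 / 111 = 0.50.

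**Step 2: effect on Q2.** Q2 = 1 − (squared prediction error) / (total sum of squares). With labels ±1, a prediction of zero gives Q2 = 0. A prediction leaning by c towards the wrong label gives 1 − (1 + c)², which is negative.

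**Step 3: exchangeability.** One simulation with no bread effect (300 features, one component, 40 runs, folds by sample) gave mean Q2 of −0.77, −1.46 and −2.12 at ICC 0.3, 0.5 and 0.7 for the real labels. Freely permuted labels gave −0.23 to −0.27. The two should agree when there is no effect, and they do not.

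**Step 4: detection.** 200 features, 20 shifted, 15 runs and 60 permutations per row. Validation by sample is compared with folds by participant and within-person label swaps, without participant centring.

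| Components | ICC | Shift (SD) | Q2 by sample | Q2 by participant | Detected by sample | Detected by participant |
|---|---|---|---|---|---|---|
| 1 | 0.3 | 0 | −0.75 | −0.24 | 0% | 13% |
| 1 | 0.3 | 0.3 | −0.30 | +0.06 | 0% | 93% |
| 1 | 0.3 | 0.5 | +0.13 | +0.36 | 100% | 100% |
| 1 | 0.6 | 0 | −1.61 | −0.31 | 0% | 0% |
| 1 | 0.6 | 0.3 | −0.80 | +0.08 | 0% | 93% |
| 1 | 0.6 | 0.4 | −0.48 | +0.28 | 0% | 100% |
| 1 | 0.6 | 0.5 | −0.22 | +0.39 | 7% | 100% |
| 2 | 0.3 | 0.3 | −0.44 | −0.14 | 0% | 67% |
| 2 | 0.3 | 0.5 | +0.06 | +0.26 | 100% | 100% |
| 2 | 0.6 | 0.3 | −0.85 | −0.16 | 0% | 93% |
| 2 | 0.6 | 0.4 | −0.43 | +0.08 | 20% | 100% |
| 2 | 0.6 | 0.5 | −0.04 | +0.29 | 100% | 100% |

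The Monte Carlo standard error of a 50% rate is √(0.25 / 15) = 0.13, so single cells are rough; the 13% in the first row is 2 of 15 runs. With 300 features and a 0.8 SD shift, Q2 by sample was 0.63 to 0.66 and positive in every run, with 100% detection at ICC 0.5.

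**Step 5: adding participant centring.** In a further simulation (200 features, 20 shifted by 0.3 SD, one component), validation by sample gave Q2 of −0.32 and −0.85, with 5% and 0% detection, at ICC 0.3 and 0.6. Centring and validating by participant gave +0.23 and +0.36, with 90% and 100% detection.

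**Step 6: adding feature selection.** With 300 features and folds by sample, keeping those with variable importance above 1 (an assumed threshold) chosen on all samples raised Q2 at 0.3 SD to between 0.15 and 0.40, positive in 92-100% of runs. With no effect, Q2 was +0.15 at ICC 0.3 (positive in 95%). At ICC 0.5 it averaged −0.20, yet the permutation test falsely rejected in 65% of 20 runs. At ICC 0.7 it stayed negative (about −0.8 to −0.9) and the test did not reject.

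**The case against.** A reader might infer that the plan validates by sample, and that a real metabolome effect will therefore be rejected by construction. The article does not support either step.

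- The unit of folds and permutations is not stated. A full plan could group by participant, and a condensed article may leave that out.
- No Q2, CV-ANOVA or permutation cut-off is given, so there is no stated rule by which a model is rejected. CV-ANOVA itself was not simulated.
- The loss is mainly for weak effects, and the article gives no metabolite effect size, ICC or number of features that would place this trial there.
- The selection and re-validation round belongs to the same pipeline and can push Q2 the other way.
- The univariate tests are not made conditional on a valid PLS-DA model, and organic and bile acids are also measured by targeted assays. Q2 is not the only route to a metabolome result.

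All of this stands and limits the claim. It does not remove the point. The article does more than omit detail: it names a method on values that are not centred by participant and pairs it with a rank sum test, which is an independent-samples test, while naming a paired test for the primary outcome. Nor does an opposing upward bias repair the downward one; two uncontrolled biases leave the validation hard to interpret.

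**Conclusion.** The point holds in a conditional form. The metabolome PLS-DA as described does not use the pairing that the crossover provides. If cross-validation and permutation are by sample, Q2 is biased downward, the permutation reference is not exchangeable with the real labelling, and weak effects can be missed: 0-5% detection at a 0.3 SD shift, against 67-100% when validated by participant, with or without centring. Larger effects are mostly still found: at 0.5 SD, detection by sample was 100% in every setting tried except one component at ICC 0.6, where it was 7%. With feature selection outside the folds, the net direction for the full pipeline is not fixed, and false positives are possible.

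The sizes rest on the assumed feature count, independence of features, ICC, effect size and number of folds, and on few runs per cell. Only secondary outcomes are concerned. The plan should be changed, but the primary outcome is untouched.

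**What to change.** For both the between-bread and the within-bread contrasts:

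1. Use multilevel PLS-DA: subtract each participant's own mean before fitting, or model within-person differences.
2. Keep all samples of a participant in the same cross-validation fold.
3. Permute by swapping labels within participant.
4. Carry out the variable-importance selection inside the folds.
5. Judge the model against that permutation distribution rather than by the sign of Q2. In the two-component rows at 0.3 SD above, Q2 by participant was still negative although the permutation test detected the effect in 67-93% of runs.

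The cost is revised wording and re-analysis; no new data are needed. Participants with only one of the paired samples drop out of these models.

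### The second-round PLS-DA check cannot detect overfitting: features are chosen by a label-based score before the rebuilt models are re-assessed, and no hold-out or in-fold selection is stated

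*Protocol article*

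**What the plan says.** The metabolome part of the Statistical Analysis Plan section of the protocol article sets out a sequence.

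1. PLS-DA is the tool for finding metabolites: "The partial least squares projection discriminant analysis (PLS-DA) model will be performed to identify metabolites using SIMCA".
2. The first models are checked in two ways: "The PLS-DA models will be subject to 100-fold permutations to evaluate performance", and "the models will be validated using the predictive ability of the model (Q2) and the ANOVA testing of cross-validated predictive residuals".
3. Features are then picked, new models built, and these re-assessed: "The most discriminating features will be selected for building PLS-DA models. These models will be again subjected to prediction accuracy and overfitting assessment".
4. The re-assessment consists of CV-ANOVA, together with "comparison of the Q2 afterward".
5. The picking rule is the VIP score: "Features will be selected based on their variable importance in the projection score".

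No hold-out set, external set or selection within cross-validation folds is mentioned, and no VIP cutoff is given. The plan does not say that failing step 2 stops steps 3 and 4. Univariate tests of metabolites and lipids with FDR correction are planned alongside.

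**The concern.** A VIP score measures how much a feature contributes to separating the two breads, so it is computed from the bread labels. If it is computed once on all samples, every sample that later serves as a cross-validation test case has already influenced which features are in the model. Features that separate the groups by chance in this dataset are kept, and they go on separating the same samples when these are left out one fold at a time. The second assessment is described as guarding against overfitting, but it cannot see overfitting that arose at the selection step. Comparing Q² before and after selection adds to the problem, because selection raises Q² even when nothing is there.

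Fecal and plasma metabolites are named secondary outcomes. The profiling is untargeted and 56 participants are in the analysis, so features probably far outnumber samples, which is where this bias is largest. At stake is whether the Q², accuracy and CV-ANOVA P value reported for the reduced models can be taken as evidence of a bread effect.

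**Working it through.** The protocol gives no figure for this point, so there is none to reproduce. The check is a simulation with no bread effect at all.

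**Inputs from the document.** 56 participants in the analysis (Results), each eating both breads, hence at most 56 × 2 = 112 post-intervention samples; untargeted profiling (fecal Metabolome section); the step order above.

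**Assumed, because the article does not give them.** 500, 2000 or 5000 features; 1 or 2 PLS components; 7 folds, with both samples of a participant in the same fold; selection by VIP>1, VIP>1.5 or the top 50. The base case is 2 components, top 50 kept and a within-person correlation of 0.5.

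**Formulas.** With PRESS the sum of squared cross-validated prediction errors, SST the total sum of squares, A components and n samples:

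- Q² = 1 − PRESS/SST
- CV-ANOVA: F = [(SST − PRESS)/2A] / [PRESS/(n − 1 − 2A)], which equals [Q²/(1 − Q²)] × (n − 1 − 2A)/2A

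For n = 112 and A = 2 the multiplier is (112 − 1 − 4)/4 = 26.75. The 5% critical value of F on 4 and 107 degrees of freedom is 2.46, so P<.05 needs Q²/(1 − Q²) > 2.46/26.75 = 0.092, that is Q² above about 0.084. A small upward bias is enough to pass: Q² = 0.10 gives F = (0.10/0.90) × 26.75 = 2.97 (P about .02), and Q² = 0.43 gives F = (0.43/0.57) × 26.75 = 20.2.

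**Base case, pure noise, features independent of one another.** Ranges cover repeated, separately coded runs.

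| Features | Mean Q², selection on all samples | Mean Q², selection inside folds |
|---|---|---|
| 500 | +0.24 to +0.27 | – |
| 2000 | +0.42 to +0.45 (accuracy 83%) | −0.42 to −0.47 (accuracy 49% to 50%) |
| 5000 | +0.50 to +0.51 | – |

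After selection on all samples, CV-ANOVA gave P<.05 in 95% of runs at 500 features and 100% at 2000. Where the two samples of a person were also simulated as uncorrelated, median Q² was higher, 0.48 to 0.88 across the component and VIP settings, with P<.05 in 100%.

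**Strongly correlated features.** With 2000 features sharing 10 latent factors, median Q² after selection was 0.10 to 0.32 and P<.05 occurred in 77% to 100% of runs, depending on components and cutoff. Under another correlated setting, mean Q² was +0.03 to +0.10 and P<.05 occurred in 30% to 58%. Both stay far above a nominal 5%.

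**Selection repeated inside each training fold.** Median Q² was −0.04 to −0.47 and P<.05 occurred in 0% to 4% of runs.

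**First-round model, all features, same noise.** Median Q² was −0.02 to −0.44 and P<.05 occurred in 0% to 6% of runs.

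**Permutation test.** With 100 permutations in 40 null datasets (500 features, VIP>1, 1 component), holding the selected features fixed gave P<.05 in 100% of datasets. Repeating the selection within each permutation gave 5%.

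**The case against.** The strongest reply is that the plan has two rounds of checks, and the first is sound. The full model is assessed before any selection, noise rarely passes there, and the planned Q² comparison means both values will be available. This stands, and it confines the point to the second round. It does not remove it, because the plan does not make the first round a condition for building or reporting the reduced models.

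A reader might infer that pure noise is bound to pass all the validation checks, or that the trial will end up declaring false metabolite effects. The documents do not support either. The first round is unbiased in this respect. Metabolite and lipid differences are also tested one by one with FDR correction, and a noise feature with a high VIP score does not become significant by that route. Passing the second round is close to certain only when features are weakly correlated.

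Selection on all samples is itself read from the order of steps and the absence of any stated split; the article does not say so in words.

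Two further criticisms are tempting and should not be made. The article is silent on how folds are formed, which a condensed article may leave to the full plan, and the simulations kept each participant in one fold anyway. The number of permutations is stated for the first-round models. With 100, the smallest attainable P value is 1/101, about .01, which suffices for the .05 and .10 thresholds the plan uses.

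**Conclusion.** The point holds for the rebuilt models only. In the stated order, their Q², accuracy and CV-ANOVA are biased upward and cannot serve as an assessment of overfitting. On noise, Q² after selection averages about +0.25 to +0.5 with independent features (base case), and CV-ANOVA is significant in about 95% to 100% of runs. With strongly correlated features the range is about 0 to +0.3 and 30% to 100%. In-fold selection brings Q² below zero and the false-pass rate to 0% to 4%.

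The sizes rest on the assumed feature count, correlation structure, number of components, folds and selection cutoff. Average Q² after selection was above zero in every setting reported here. The first-round check, the FDR-corrected univariate tests and the primary microbiome composite are not affected. This should be corrected, but it concerns how secondary metabolome results are validated, not the main conclusion of the trial.

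**What to change.** Either of two changes is enough.

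- Repeat the VIP selection inside every cross-validation fold and every permutation, keeping all samples of a participant together, and report that nested Q² and CV-ANOVA for the reduced models.
- Or base any claim of validity only on the Q², CV-ANOVA and permutation test of the full model, require that model to pass before a reduced one is built, and use the selected features for display only.

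The first costs computing time and a short script outside the default software workflow. The second uses quantities the plan already produces and needs only a change of wording. Neither needs new data.

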#### Data Quality and Assurance

The researchers collecting data were trained accordingly in data collection, maintaining security and health-related confidentiality.

Due to the large amount of data to be collected, there may be an inherent risk of errors during the data entry into the data bank. All paper-based data were handled by blinded study personnel, and participants were strongly encouraged to enter survey data directly into the database via email links to the surveys and via the app to minimize this risk.

The nutrition graduates who entered the raw food and beverage diary data maintained a data entry assumption spreadsheet to ensure consistency of data entry. The study dietitian will independently audit 20% of the food diaries entered into the dietary analysis program (Foodworks Online; version 1.0) by the nutrition graduates. Diaries were checked for accuracy, consistency, and completeness. Extreme values or outliers for specific nutrients were identified and clarified by reviewing the assumption spreadsheet and raw food and beverage diary data.

A formal data monitoring committee was not required as the intervention and placebo breads in this study are considered as sufficiently low risk that no harm is anticipated to occur beyond the risks of standard care and everyday life.

Data monitoring occurred through weekly meetings of the research team. The unblinded research team maintained concealment.

